### Intervention description {11a}

#### Intervention

DBED [10] is a 3-step method (Fig. 1) starting with both parents and kindergarten teachers completing the Early Worry Questionnaire (EWQ) (Step 1) as a preparation for the biannual parent-teacher conference. The EWQ contains 37 questions that systematically map possible concerns for the individual child’s wellbeing and development. When a concern is stated, the respondents are asked to suggest possible causes in an open-ended follow-up question. Step 2 is the parent-teacher conference where they compare their answers from the EWQ and discuss whether there is a reason for concern or not. In case of consensus of concern, a discussion of possible further actions should follow (Step 3), such as closer observation of the child, simple educational interventions (e.g., playgroup), or referral to more specific external assessment or services. During feasibility testing (*N* = 153) of the method, DBED was well accepted by parents and teachers [10]. Preparation before parent-teacher conferences by completing the EWQ facilitated a more active involvement of the parents in the dialogue. They also more often presented previously unspoken concerns for their child [10].

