The factor structure of EWQ as reported by parents and teacher, respectively, prior to the parent-teacher conference and as reported DBED concluded concern from the parent-teacher conference, primarily at baseline, but also at the following half-year registrations for comparative reasons.Agreement between (i) reported concern and DBED concluded concern, respectively, measured by total EWQ score and EWQ sub-scores, and (ii) mental health measured by SDQ Total difficulties score, each sub-scale score, and two SDQ impact scores, respectively, at baseline.Agreement between parent’s and teacher’s mental health report measured by agreement between parent and teacher SDQ scores and the above mentioned SDQ impact scores at baseline and after 12, 24, and 36 months, respectively.Agreement between parents and teacher in possible concerns for the child measured by percentage of EWQ items rated as the three different response options, respectively (satisfied; a bit uncertain; concerned), at baseline and after 12, 24, and 36 months, respectively).Change from reported to concluded concern during the parent-teacher conference measured similarly as the preceding outcome.Satisfaction with the DBED after all parent-teacher conferences measured by the study-specific satisfaction questionnaires for parents and teachers, respectively.Predictors of mental health change during the 5-year follow-up. Mental health is measured by SDQ-scores (Total difficulties score, sub-scales and impact scores) and the predictors (at baseline) are measured by:◦ Parent’s educational level◦ Satisfaction with economic situation◦ Social support◦ Single parenting◦ Close relatives in the vicinity◦ Norwegian language at home?◦ Is Norway parent’s country of origin?◦ Major illness or handicap◦ Level of parental concern◦ Level of teacher concern◦ Level of DBED concluded concern◦ Parent-teacher agreement after the parent-teacher conversation at baseline◦ Level of parental stressPredictors of parental and teacher concern, respectively. Concern is measured by parent and teacher EWQ total score at baseline and changes throughout the 3-year follow-up period in kindergarten, and the predictors are the same as for mental health change.Predictors of parental stress. Parental stress is measured at baseline and changes throughout the total follow-up period of 5 years, and the predictors are the same as for mental health change (except parental stress).Predictors of parent satisfaction. Parent satisfaction is measured by the study-specific satisfaction questionnaire at baseline and changes throughout the 3-year follow-up period in kindergarten, and the predictors are the same as for mental health change.

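### The predictor rule for parental and teacher concern makes no exception for the outcome's own baseline score, and lets measures taken after the conference predict the level recorded before it

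*Protocol article*

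**What the plan says.** In Outcomes {12}, the process outcomes include an item on predictors of mental health change, for which "the predictors (at baseline) are measured by" 13 listed variables. Eight are background items: education, economic satisfaction, social support, single parenting, relatives nearby, home language, country of origin, and major illness or handicap. The other five are "Level of parental concern", "Level of teacher concern", "Level of DBED concluded concern", parent-teacher agreement following the baseline conference, and parental stress.

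The next item turns to concern, with parents and teachers as separate outcomes: "Concern is measured by parent and teacher EWQ total score at baseline". On how that score develops later, and on which variables are to explain it, the item reads: "changes throughout the 3-year follow-up period in kindergarten, and the predictors are the same as for mental health change". It states no exception.

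The item after that, on parental stress, uses the same device but removes the outcome from its own list: "the predictors are the same as for mental health change (except parental stress").

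The section on assessment and collection of outcomes {18a} makes the EWQ the instrument for concern, used in the intervention group only. Parents and teachers complete it before the conference, and the teacher scores the conclusions afterwards. The Intervention section explains the link: "Step 2 is the parent-teacher conference where they compare their answers from the EWQ". Statistical methods {20a} assigns conditional latent growth curve models to all the predictor questions and does not qualify the list.

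**The concern.** A predictor list written for one outcome (SDQ) is reused for another outcome (EWQ concern) that is itself on the list. Two problems follow for the baseline level of concern.

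- **Self-prediction.** The baseline EWQ score of the informant under study stands on both sides of the model.
- **Reversed time order.** Concluded concern and post-conference agreement come out of a conference that starts from the completed EWQs. They are consequences of baseline concern and cannot explain it.

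The abstract names socio-demographic predictors of parent and teacher concern as something the project will assess. Those are the coefficients that a self-term or a downstream term would remove or bend.

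**Working it through.** The plan gives no figure to reproduce. The check sets the outcome definition, the list and the timing side by side.

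**Inputs.** Outcome definition and 13-item list: Outcomes {12}. Instrument and order of completion: section {18a}. Link between the EWQ and the conference: Intervention section. Six half-yearly EWQ rounds: participant timeline {13}. Model class: section {20a}.

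**Status of each concern-related term, by model**

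| Listed term | Baseline level of parental concern | Baseline level of teacher concern | Later change in either |
|---|---|---|---|
| Parental concern | the outcome itself | other informant, admissible | see step 4 |
| Teacher concern | other informant, admissible | the outcome itself | see step 4 |
| DBED concluded concern | arises after the outcome | arises after the outcome | precedes it, admissible |
| Post-conference agreement | arises after the outcome | arises after the outcome | precedes it, admissible |

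**1. Count.** In each baseline-level model, 1 self-term + 2 later terms = 3 of 13 are misplaced, which leaves 13 − 3 = 10. For change, only the outcome's own baseline score needs separate handling, which leaves 13 − 1 = 12.

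**2. Self-term.** Let Y be the informant's baseline EWQ total and X the other predictors. Fitting Y = a + bY + cX + e by least squares gives a = 0, b = 1, c = 0, zero residual and R² = 1, whatever X is. In a growth model the first EWQ score would be both an indicator of the intercept factor and a predictor of that factor.

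**3. Downstream term.** As a simple illustration under my own assumptions, let Y = βX + u and let concluded concern be C = Y + v, with u and v independent. Regressing Y on X and C gives X the coefficient β × var(v) / [var(u) + var(v)]. The multiplier lies between 0 and 1 and falls towards 0 as the conclusion follows the reported concern more closely. If C also depends on X directly, the shift can go further and need not be simple attenuation. The documents give no variances, so no figure can be attached.

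**4. Change.** The conference in the first round precedes the five later EWQ rounds (6 − 1 = 5), so concluded concern and agreement from it are correctly ordered as predictors of change. An informant's own baseline score as a predictor of that informant's change is not an identity. It does duplicate what the growth model already carries through the intercept and its association with the slope. The other informant's baseline score has neither problem.

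**The case against.** The strongest reply is that this is a dropped parenthesis in a condensed article. The authors plainly know the rule, because they apply it to parental stress. The abstract describes the aim as socio-demographic, and an exact identity would be noticed as soon as the model was fitted. The article also never says that all 13 predictors enter one model. If they are examined one at a time, the self-term does no harm to the others.

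Much of this stands. It makes an oversight the likely explanation, and it makes the damage to the background coefficients conditional on joint entry. It does not remove the point. The article does not leave the predictor set to a later document: it states the set, and the statement is wrong for this outcome. The downstream terms would also not announce themselves as an identity does. A model with concluded concern as a predictor of baseline concern fits without complaint and returns altered coefficients.

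A reader might infer more: that all four concern-related terms are invalid throughout and should be struck from every concern model. The documents do not support that. Parents and teachers are separate outcomes, so only one listed term per model is the outcome itself. Using one informant's concern to predict the other's is legitimate. Concluded concern and agreement come before every later EWQ round and are proper predictors of change. In an intervention built on comparing the two informants' answers, deleting them everywhere would discard real process questions.

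**Conclusion.** The point holds for the baseline level of concern. Each model contains one self-predictor and two predictors that arise after the outcome: 3 of the 13 listed terms. Nothing in sections {18a} or {20a} corrects this.

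The conclusion rests on two assumptions. First, the level of concern in the predictor list is the same pre-conference EWQ score that serves as the outcome; the article names no other measure of it. Second, the loss or distortion of the socio-demographic coefficients requires that the terms be entered jointly, which the article neither states nor rules out. It would therefore go too far to say that those coefficients will certainly be zero.

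The reach is limited to one process outcome, measured in the intervention arm. The SDQ comparison, the comparisons of parental stress and time to support, and the sample size are untouched. The correction is worth making because the rule is wrong as stated and easily put right before analysis.

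**What to change.** Add an exception to the concern item in Outcomes {12}, parallel to the one for parental stress. For example:

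*The predictors are those listed for mental health change, except that (a) the model for each informant's concern omits that informant's own baseline EWQ score as a covariate, initial level being represented by the growth-model intercept and its association with the slope; and (b) DBED concluded concern and post-conference agreement at baseline are used only as predictors of change after baseline, not of baseline level. The other informant's baseline concern is retained.*

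When this is fitted as one growth model, concluded concern and agreement should be left free to covary with the intercept (or be regressed on it), because they are related to the baseline level even though they do not explain it.

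The cost is one sentence and a matching model specification, with no new data and no change to the design. The change gives up only the use of the two post-conference terms to explain baseline level, and the use of a score to explain itself. The cross-informant questions and the questions about later change are kept.

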
### Participant timeline {13}

**Table Tabb:** 

	Study period											
Year^**a**^	0	1			2		3		4		5	
Timepoint (months after start of kindergarten year)	10	3	4–6	10–12	4–6	10–12	4–6	10–12	4–6	10–12	4–6	10–12
Randomization	x											
**Enrolment**												
Informed consent^b^		x										
**Intervention**												
DBED^c^			x	x	x	x	x	x				
TAU^c^			x	x	x	x	x	x				
**Assessment**												
Baseline demographics and health information			x									
EWQ			x	x	x	x	x	x				
Conclusions DBED			x	x	x	x	x	x				
Actions^d^			x	x	x	x	x	x				
SDQ^e^			x	x	x	x	x	x	x	x	x	x
PSS			x	x	x	x	x	x	x	x	x	x
**Process evaluation**^f^												
Parent and teacher satisfaction^g^			x	x	x	x	x	x				
Interviews of parents and kindergarten teachers				x				x				
Audio recordings of parent-teacher conferences				x				x				

^a^Kindergarten year starts July 1^st^

^b^Informed consent is obtained a few weeks before intervention

^c^DBED and TAU are accomplished every 6 months

^d^Specified supportive actions within or outside the kindergarten, differentiated between old and new ones

^e^Data are collected 1 to 3 weeks after the intervention, but the scores relate to the child’s performance during the last 6 months

^f^Several of the questionnaires intended for primary and secondary outcomes, such as EWQ, Conclusions DBED, SDQ, and PSS, are also used in the process evaluation; see the “Outcomes {12}” section

^g^Includes also free text comments related to responder’s experiences of participating in the DBED method

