**Methods:**

Ten kindergartens will be randomly selected to implement DBED, while ten will act as controls, offering ordinary parent-teacher conferences. Parents of at least 100 + 100 children will be recruited. The primary outcome will be children’s mental health in the intervention group as assessed by the Strengths and Difficulties Questionnaire (SDQ), during the 5-year follow-up, compared to the control group. Secondary outcomes will be (i) the effect of DBED on parental stress as measured by the Parental Stress Scale (PSS) and (ii) time to activation of support, as measured by the duration from the first parent-teacher conference to activation of any support, comparing the two groups. We will also assess (iii) socio-demographic predictors for mental health development, parent and teacher concern for the child, parental stress, and parent satisfaction with DBED, (iv) screening properties of DBED compared to SDQ, and (v) social validity of DBED as measured by user-satisfaction questionnaires and interviews with both parents and teachers.

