### Outcomes {12}

Primary outcome:

Effect of DBED on mental health measured as the difference between intervention group and control group in Total difficulties score of SDQ. Measurement scores will be recorded every sixth month during the entire 5-year project period (i.e., child-age 3 to 8 years) as repeated measures. SDQ sub-scores and two impact scores (difficulties in general and impact on four areas of daily functioning) will be analyzed. The primary endpoint will be during the last 3 months in kindergarten before the child starts school, giving total change over six time points of measurements. The secondary endpoint will be during the last 3 months in the second school year (10 time points of measurements).

Secondary outcomes:

Effect of DBED on time to initiated locally available supportive action analyzed as the difference in time (months) from inclusion to activation of such actions between the intervention group and control group as mean time (months) from inclusion to activation of such actions. This outcome will indicate if DBED may lead to earlier supportive actions for children.Effect of DBED on parental stress analyzed as the difference in total scores of the PSS between the intervention group and the control group [12]. Measurements will be recorded every sixth month during the project period. This outcome will indicate if DBED may lead to less or more parental stress and more or less self-confident parents.

Process outcomes:

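### Time to support is compared in months, but the article describes actions only as old or new at six half-yearly waves and names no method for times known to within about six months

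*Protocol article*

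**What the plan says.** Outcomes {12} lists time to supportive action as a secondary outcome, "analyzed as the difference in time (months) from inclusion to activation of such actions", summarised as a mean per arm. It is meant to show whether DBED brings support forward.

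The table under Participant timeline {13} places the Actions item at six waves, two in each of the three kindergarten years, and at none of the school waves. Footnote d gives its content: "Specified supportive actions within or outside the kindergarten, differentiated between old and new ones". Footnote c adds that "DBED and TAU are accomplished every 6 months", so both arms hold conferences on the same rhythm.

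Intervention description {11a} places decisions on action at the DBED conference: once parents and teacher agree that there is a concern, "a discussion of possible further actions should follow (Step 3").

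Section {18a} says that trial data come only from online questionnaires completed by parents and teachers, and refers to Additional file 2 for the item on supportive actions. Section {20a} says that this outcome is analysed like the primary one, that is, by latent growth curve models. Cox and Weibull models appear only in a conditional sentence on checking assumptions.

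**The concern.** The outcome is stated to the month, but the record that the article describes is coarser. An action that is new at one wave is known only to have begun since the previous wave, about six months before. Some rule must turn that into a number of months, and the article gives none.

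If the wave of report serves as the date, each time is overstated by the lag between the true start and the next report. A lag of the same average size in both arms would cancel. It need not be the same. DBED has an explicit step for deciding on action at the conference, while {6b} calls the usual conference loosely defined. Starts may therefore cluster around conferences differently in the two arms, and the difference in mean lag would then appear as a treatment effect on timing.

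The analysis named does not help. A growth curve describes a repeated score, not the time to a first event, and a mean time is undefined for children who never receive an action.

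**Working it through.** **Plan's own figure.** There is none to reproduce. The 95% power in Sample size {14} concerns the SDQ. No expected difference or power is given for time to support.

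**Inputs from the article.**
- Six waves, in months 4–6 and 10–12 of each kindergarten year (timeline table).
- Nominal gap between waves g = 6 months. The windows allow 10 − 6 = 4 to 12 − 4 = 8 months.

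**Assumptions, not in the documents.**
- True times to support have the same mean in both arms, and each action is dated at the wave that first reports it.
- A share p of DBED actions and a share q of control actions start at the conference and are reported at that same wave. The rest start evenly between waves.
- The form is completed at the conference (no delay).

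**Formula.** Lag = wave of first report − true start. Evenly spread starts have mean lag g/2, and starts at the conference have lag 0.
- Mean lag, DBED: (1 − p) × g/2
- Mean lag, control: (1 − q) × g/2
- Spurious lead for DBED: (g/2) × (p − q)

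**Results.**

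| Pattern | Gap (months) | Spurious DBED lead (months) |
|---|---|---|
| p = 100%, q = 0 | 6 | 3 × 1.00 = 3.0 |
| p = 100%, q = 25% | 6 | 3 × 0.75 = 2.25 |
| p = 100%, q = 50% | 6 | 3 × 0.50 = 1.5 |
| p = 100%, q = 75% | 6 | 3 × 0.25 = 0.75 |
| p = q | 6 | 0 |
| p = 80%, q = 50% | 6 | 3 × 0.30 = 0.9 |
| p = 100%, q = 0 | 4 | 2.0 |
| p = 100%, q = 0 | 8 | 4.0 |
| DBED at conference; control in first month after it | 6 | 6 − 0.5 = 5.5 |
| DBED 0.5 month after the form; control evenly spread | 6 | 3.0 − 5.5 = −2.5 |

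Simulation with 400,000 draws gave 3.00, 5.50 and −2.50 for the first row and the last two rows. A constant control hazard of 0.01 to 0.06 per month, instead of even starts, gave mean lags of 3.0 to 3.2 months.

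**Delay between conference and form.** With a delay d, an action started at the conference has lag d, and the difference becomes (g/2 − d) × (p − q). With d = 0.5, the first row falls to 2.5 months. The 1 to 3 weeks in footnote e belongs to the SDQ row, so no delay is documented for Actions.

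**Midpoint dating.** This does not cure the problem. In the first row, DBED actions would be dated 3 months too early and control actions would be right on average, which leaves the same 3 months.

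**Analysis by wave.** Suppose 6% of children in each arm start an action per cycle, DBED exactly at the wave and controls evenly within 3 months either side. Mean times are equal. At the first follow-up wave, 6% of DBED children but only 6% × ½ = 3% of controls in that cycle have started. A by-wave analysis needs no invented date, but it still depends on when actions fall relative to the form.

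**The case against.** The strongest objection is that the instrument has not been seen. Footnote d is a one-line table note and does not exclude a date field, and form details and dating rules are commonly left to a supplement or an analysis plan. A reader might infer that actions are recorded only as old or new and will be dated by wave. The article says neither. This stands, and it makes the point conditional on the form. It does not remove the point, because an analysis plan cannot recover a date that was never collected.

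A reader might also infer a bias that always favours DBED. The documents do not support that. Step 3 is a discussion, and its possible results include observation and referral, so activation can come later. An action that starts just after the form is first reported at the next wave, which makes DBED look late. Control conferences are also six-monthly, and {30} says that the possible actions are the same in both arms. Equal clustering gives no artefact.

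Nor is 3 months a ceiling. It is a mean under one assumed pattern, and other patterns exceed it.

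Finally, a reader might worry about zero durations in a Weibull model, since the abstract counts from the first conference ("the duration from the first parent-teacher conference to activation of any support"). Outcomes {12} counts from inclusion, consent is obtained a few weeks before the intervention, and survival models are only conditional. That worry is not established. Nor does the article rank this outcome above the other secondary outcome, parental stress.

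**Conclusion.** The point holds in conditional form. The article states the outcome in months, describes a record that places a start only within about six months, and names no interval-censored or grouped-time method. If no start date is collected and months come from the wave of report, the comparison can be distorted by an amount that is large for an outcome measured in months. Illustrative values are 3 months towards DBED, 0, and 2.5 months against DBED. They rest on assumed patterns of when actions start, for which the documents give no data. Neither the direction nor a maximum can be stated. If the form already asks for a start date, all that is missing is a sentence saying that the analysis uses it.

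**What to change.** 1. Check the Actions item in Additional file 2. If it asks when each action started, state that the months outcome is computed from that date.
2. If it does not, add month and year of start at the remaining waves, ask for it retrospectively for actions already reported, and base the outcome on it. This costs one form field and a sentence in the analysis plan. Recall for past actions will be imperfect and worsens with each wave, so it should be done soon.
3. If no date can be obtained, drop months as the unit. Analyse first new action by wave with an interval-censored or discrete-time (complementary log-log) model that accounts for kindergarten and keeps children with no action as censored. Limit the conclusion to support by a given wave. The cost is coarser time resolution, and the report should say that the by-wave comparison still reflects when actions fall relative to the form.

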### Sample size {14}

The participating children are expected to represent the general population and are not a clinical sample with a presumed high level of mental symptoms. Hence, even if DBED will have a promoting effect on mental health among the children, the difference between the intervention and the control group will probably be small. In the absence of other similar studies, we chose a difference of 0.8 in SDQ Total Difficulties Scale score based on discussions in the project group. Then, we powered the study to be able to detect such a difference between the implementation and the control group. Mplus was used for Monte Carlo simulations assuming the participation of 20 kindergarten (clusters) with ten participating subjects within each cluster and a baseline SDQ mean 5.5 (English norm data: 5.7) SD = 5.5 (σ^2^_within_ = 30.25). The group differences were represented with a predictor of the slope factor in a latent growth curve model. The model assumed normative stability in the controls (mean change = 0.0) and a reduction of −0.8 in the intervention group during the total period. Group sizes were set to be equal. Some between-cluster variation was specified in the intercept factor (σ^2^_between_ = 2.0) to give expected ICC = 0.10 in the six outcome variables over time. The attrition was assumed to be up to 25%. The number of replications was 1000. To achieve the difference of 0.8 with a sample size of *n* = 100 in each group, the statistical power for the testing of group difference was found to be 95%.

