Baseline information (demographics, social support, health related information)◦ Parent’s educational level (values 0–3)◦ Satisfaction with economic situation (Visual analogue scale, values 0–10)◦ Social support, adapted from the PIRM study [15] containing nine items. See Additional file 2 for details.◦ Single parenting (values 0–1)◦ Close relatives in the vicinity (values 0–1)◦ Norwegian language at home? (values 0–1)◦ Is Norway parent’s country of origin? (values 0–1)◦ Major illness or handicap (child) (values 0–1)EWQ (only for the intervention group) [10] is a novel tool for assessing parents and kindergarten teachers’ possible concerns for a child. The psychometric properties of EWQ are not yet established but will be subject to analyses in the present study. We will apply the total EWQ score (values 0–74) and EWQ sub-scores (five sub-scores, values from 0–10 to 0–18). EWQ will be scored in two different situations:◦ Prior to the parent-teacher conference, completed by both each parent and teacher.◦ As conclusions after the parent-teacher conference, completed by teacherSDQ, 2–4 years version [16] is a standard screening tool for mental health symptoms among young children with well-established validity [16] and psychometric properties [17]. We will apply SDQ Total Difficulties Scale score (values 0–40), each sub-scale score (values 0–10), and two SDQ impact scores (values 0–3 and 0–12, respectively) addressing difficulties in general and in four different areas of daily functioning.PSS is an 18-item questionnaire (values 0–72) assessing parents’ feelings about their parenting role, exploring both positive aspects (e.g., emotional benefits, personal development) and negative aspects of parenthood (e.g., demands on resources, feelings of stress) [12].User satisfaction with the DBED method (only for the intervention group) measured after all parent-teacher conferences by study-specific questionnaires, see Additional file 2.◦ Parent questionnaire: five items (values 0–15) and optional free text response◦ Teacher questionnaire: seven items (values 0–21) and optional free text responsePossible supportive actions initiated, see Additional file 2.How specific questionnaires relate to the primary, secondary, and process outcomes, respectively, is described in the “Outcomes {12}” section. Collection of qualitative data for process outcomes is described in the “Data management {19}” section.

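### The SDQ wave used as baseline is collected 1 to 3 weeks after the first conference, so any effect or rating shift already visible then is absorbed into the starting level

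*Protocol article*

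**What the plan says.** **Timing.** The table under Participant timeline {13} puts the first SDQ in the same column as the first DBED or TAU conference (months 4–6 of year 1). Footnote e, attached to the SDQ row, reads "Data are collected 1 to 3 weeks after the intervention" and adds that the scores cover the preceding 6 months. The only earlier contact with participants is consent: "Informed consent is obtained a few weeks before intervention". No SDQ stands in that column. The conference then recurs: "DBED and TAU are accomplished every 6 months".

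**Use as baseline.** Sample size {14} gives the starting SDQ mean of 5.5 as a baseline value and states: "The group differences were represented with a predictor of the slope factor in a latent growth curve model". Outcomes {12} defines the primary endpoint as total change over six measurements. Statistical methods {20a} speaks of differences in trajectories and does not say whether arm also predicts the intercept.

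**Screening aim.** The EWQ is completed "Prior to the parent-teacher conference, completed by both each parent and teacher". Outcomes {12} compares reported and concluded concern with the SDQ total score, "each sub-scale score, and two SDQ impact scores, respectively, at baseline".

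**PSS.** The PSS row carries no footnote e. Outcomes {12} says only "Measurements will be recorded every sixth month during the project period".

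**The concern.** The first SDQ comes after allocation, after teacher training and after the first conference; in the DBED arm it also comes after the 37-item EWQ. Change measured from it is change from a treated state. Two things can then go wrong, in opposite directions.

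- A true early benefit already present at wave 1 is not counted in the slope.
- If DBED makes raters report more difficulties for a while, the later return to usual reporting looks like improvement.

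The second route has some support in the protocol. The trial is open-label, the raters are the parents and teachers who took part in the conference, and only DBED raters have just filled in and compared concern items. Intervention description {11a} reports that parents in the feasibility study more often raised concerns they had not voiced before.

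Randomisation does not settle the matter. Kindergartens were allocated before parents were recruited, and the two arms received different information (Concealment mechanism {16b}). Without an SDQ before the first conference, a wave-1 arm difference cannot be divided into selection and first-conference effect.

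**Working it through.** **Inputs.** Six kindergarten waves, taken as equally spaced (timeline); target difference 0.8 points over the total period; 100 children per arm; total variance 30.25; attrition up to 25%; stated power 95% (all Sample size {14}); threshold 0.05 (Statistical methods {20a}), taken as two-sided.

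**The stated power.** The protocol gives no within-child correlation r, residual variance or slope variance, so 95% cannot be reproduced. In a random-intercept growth model with 0.8 as total change, power is 18% to 78% for r from 0.3 to 0.9 without attrition, and 15% to 68% with 25% attrition. Reaching 95% needs r of about 0.94 to 0.95. The point here does not depend on this. The standard error that 95% power implies is 0.8 / (1.960 + 1.645) = 0.222; at r = 0.6 with 25% attrition it is 0.65. Both are used below.

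**Weight of wave 1.** Code the waves −2.5, −1.5, −0.5, 0.5, 1.5, 2.5. The sum of squares is 17.5. The weight of wave 1 on the least-squares slope is −2.5/17.5 = −0.143 per interval. Over five intervals this is −0.714. The six weights on fitted total change are −0.714, −0.429, −0.143, 0.143, 0.429 and 0.714.

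**Effect of a DBED-only rating rise of 0.5 points at wave 1** (size and course are assumptions; no true effect):

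| Course of the shift | Factor | False total change |
|---|---|---|
| Gone by wave 2 | −0.714 | −0.36 |
| Halves at each wave | −0.897 | −0.45 |
| Fades linearly to zero at wave 6 | −1.000 | −0.50 |
| Persists unchanged | 0 | 0 |

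The first row is 0.357/0.8 = 45% of the target. A shift that grows linearly from 0 to 0.5 gives +0.50, against DBED. Under the three fading courses, a rise of 0.8/0.714 = 1.12, 0.8/0.897 = 0.89 or 0.8/1.000 = 0.80 points would imitate the whole target.

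**Chance of a false finding.** For the first row, the two-sided rejection rate is 36% at SE 0.222 and 8.5% at SE 0.65.

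**Alternative contrasts.**

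- *Model-implied arm difference at wave 6.* Wave 1 has weight 1/6 − (2.5 × 2.5)/17.5 = −0.190, so the 0.5-point transient rise contributes −0.10 instead of −0.36. A persistent 0.5-point shift, or a stable selection difference of that size, enters in full: 0.5/0.8 = 63% of the target.
- *Slope without wave 1.* A wave-1-only rise contributes nothing. A rise that halves each wave still does: the slope is 0.5 × (−2 × 0.5 − 0.25 + 0.0625 + 2 × 0.03125)/10 = −0.056 per interval, or −0.28 over five, against −0.45 with wave 1. A linear fade is unchanged at −0.50. The sum of squares falls from 17.5 to 10, so with a random intercept and no attrition the slope SE rises by √1.75 = 1.32.

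**The case against.** **The recall window.** Scores refer to the last 6 months, so only 1 to 3 of about 26 weeks (4% to 12%) follow the first conference. This stands for true change in the child: little of it can show at wave 1. Benefit through supportive actions that emerges later appears from wave 2 and stays in the slope. A reader might infer that the slope discards the whole first-conference effect; the documents do not support that. The window does not, however, prevent a change in how raters report.

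**The trigger recurs.** The EWQ, the conference and then the SDQ are repeated at all six kindergarten waves. If DBED raises ratings each time by the same amount, the slope is unbiased. This stands: a false benefit requires the shift to fade.

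**The slope-only contrast comes from the power model.** This is correct. The analysis section does not exclude an arm effect on the intercept, and an article may leave that detail to the full protocol or analysis plan. Such a term would show the wave-1 difference but could not separate it from selection.

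**The 0.8 points.** A reader might scale the target down for the share reached before wave 1. The sample-size text places 0.8 within the growth model over the six outcomes, so that scaling assumes an origin the protocol does not use.

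**Screening and PSS.** A reader might infer that EWQ–SDQ agreement is inflated. That is not shown: discussion could also move the SDQ away from the pre-conference EWQ. A reader might also extend the timing to the PSS. Its place relative to the conference is not stated; one can say only that no PSS column precedes the first conference round.

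**Conclusion.** The concern holds for the SDQ. As scheduled, there is no measure of the primary outcome before the first conference, and the wave treated as baseline follows it. Any first-conference effect or DBED-specific rating shift visible at 1 to 3 weeks is absorbed into the intercept. The direction of the resulting error is not fixed: towards DBED if a rating rise fades (−0.36 to −0.50 per 0.5 points, depending on the course), none if it persists, against DBED if it grows, and towards no effect if there is a true immediate benefit. The 0.5-point size is an assumption, since the protocol gives no estimate of such a shift. The weights rest on six equally spaced, equally weighted waves and a linear trajectory.

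For the screening aim, what stands is that the SDQ is completed after the raters have discussed the EWQ, so the two are not independently timed measures.

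**What to change.** **Children who have not yet had the first conference.** Send the existing online SDQ after consent and before that conference, at the same time in both arms, and call this baseline. Do not tie it to the EWQ mailing, because controls receive no EWQ.

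**Children already measured afterwards.**

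- Relabel the measure 'wave 1 (post-conference)' and do not adjust for it as a baseline covariate.
- Let arm predict both intercept and slope, and report the wave-1 arm difference.
- Pre-specify two sensitivity analyses: the model-implied arm difference at wave 6, and the slope without wave 1.
- State that the wave-6 difference also carries any selection imbalance from recruitment after allocation was known. For that reason it is a sensitivity analysis and not the new primary contrast.

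**Screening aim.** Use the pre-conference SDQ for agreement with the pre-conference EWQ where it exists. Otherwise state that the SDQ was completed after the raters had discussed the EWQ.

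**PSS.** State when it is collected relative to the conference.

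**Cost.** Earlier dispatch of an existing form, some wording and some extra analysis. Trial status gives recruitment as January 2024 to January 2025, so many first waves may already exist. Those children will lack a true baseline, and first-wave timing will be mixed between children.
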